### Treatment protocol

After being admitted to the hospital, all patients will be assessed and receive standard treatment (including surgery, if necessary) in the neurology ICU in accordance with the current guidelines [25]. Those who meet the criteria and whose representative has signed an informed consent form will be enrolled in the trial and be randomly assigned to the stimulation or non-stimulation group according to the procedure mentioned above.

The patients in the stimulation group will receive RMNS in addition to standard treatment. The electrical treatment will be delivered via a pair of lubricated 1-inch square rubber surface electrodes pasted 1 inch apart on the volar aspect of the right distal forearm over the median nerve. An electrical neuromuscular stimulator (Verity Medical Ltd., Braishfield, UK) will supply trains of asymmetric biphasic pluses at an amplitude of 15–20 mA (as tolerated) with a pulse width of 300 μs at 40 Hz ON for 20 s and OFF for 40 s, which has been proven to be well tolerated without causing pain or skin irritation. The electrical stimulation treatment will last for 8 h per day for 2 weeks. Patients assigned to the control group will continue to receive the previous standard treatment without electrical stimulation. During treatment, all patients will receive intensive care to prevent hypotension, hypoxia, intracranial hypertension and disturbance of homeostasis.

In addition to vital signs and general data, some additional data from the case report forms (CRFs) will be assessed at the beginning of the trial and during treatment. Once enrolled in the trial, the GCS, Glasgow Coma Scale Motor Part (GMS), Full Outline of Unresponsiveness (FOUR) scale, Coma Recovery Scale-Revised (CRS-R) and Disability Rating Scale (DRS) scores of each patient will be collected.

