### Study endpoint

The primary endpoint is the percentage of patients regaining consciousness 6 months after injury. The degree of consciousness can be divided into three categories: VS, MCS and consciousness (CS). The diagnosis of consciousness includes complete wakefulness and awareness of self and environment, precise comprehension and interaction, correct orientation of figures, time and location, the ability to obey commands and intact light and deep reflexes [24]. In the ACES trial, we will focus on the percentage of patients regaining consciousness 6 months after injury. This parameter indicates the long-term effect of RMNS.

The secondary endpoints are GOSE, CRS-R and DRS scores 28 days, 3 months and 6 months after injury and GCS, GMS and FOUR scores day 1 and day 7 after enrolment and 28 days, 3 months and 6 months after injury. Duration of unconsciousness and mechanical ventilation, and length of ICU and hospital stays will also be recorded as secondary endpoints.

The safety of RMNS will be assessed by the incidence of adverse events within 6 months post injury, including but not limited to (1) seizures, (2) increased intracranial pressure and (3) intracranial bleeding.

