### Data collection and follow-up

General baseline information will be collected about patients when they are sent to the emergency room and will include the following: demographics, time of admission, cause of injury, whether accompanied by multiple trauma, injury severity score, initial GCS score, initial intracranial computed tomography (CT) data including Marshall score and whether complicated by subarachnoid haemorrhage, pupillary light reflex or the need of craniotomy.

After 7–14 days of standard treatment, when the patient’s condition is stable and once he/she is enrolled and randomised, additional data will be collected, including vital signs such as blood pressure, heart rate, respiratory rate and oxygen saturation, pupillary light reflex and GCS, FOUR, CRS-R and DRS scores.

Patients in both the RMNS group and the sham group will be evaluated via GCS and FOUR scores at day 1 and day 7 of the treatment. Whether or not the coma patient regains consciousness and the date will be recorded in the CRF. Any complications will also be observed and recorded during the treatment.

Outcome assessment will be performed using the GCS, FOUR, CRS-R, DRS and GOSE at 1, 3 and 6 months. Complications during follow-up will also be assessed. If the patient is still in the hospital, the investigator may visit the patient on the ward to go through the evaluation. If the patient has been discharged, his or her legal representative will be told to come back in due time for assessment after leaving the hospital. If the patient does not arrive, the investigator will try to contact the patient or the family members by telephone. Other possible methods may also be used to explain the situation and complete the outcome assessment. If all attempts fail, no further contact will be made, and the patient will be recorded as lost to follow-up. Any death occurring either in or out of the hospital will be recorded and possible causes explored.

All the data will be collected by independent investigators who are blind to the patient’s allocation. Each local study centre will assign a specific investigator at the beginning of the trial. This investigator will be excluded throughout treatment of all the participants unless asked to do the assessment by clinicians. During the 2 weeks of RMNS treatment, the investigators will be asked to collect the data during the interval of 8-h RMNS treatment per day so as to eliminate any chance of disclosing the allocation.

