### Statistics and data analysis

#### Sample size justification

The required sample size is calculated based on the results of our previous randomised controlled trial [24]. In that study, the proportions of patients regaining consciousness in the RMNS and non-stimulation groups were found to be 59.8% and 46.2%, respectively. Thus, to detect a difference of not less than 13.6% (the difference between 59.8% and 46.2%) between the experimental group and the control group, 334 patients will be needed with an α value of 0.05 and a power of 0.8. To allow for some patients lost to follow-up, a sample size of 380 in total (190 for each group) has therefore been chosen, which gives 84% power to detect the same difference at the same significance level.

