#### Statistical analysis

Analysis will be performed in accordance with the intention-to-treat principle. All randomised patients will be included in their original assigned group regardless of the actual treatment approach they receive. Categorical variables will be described as numbers and percentages and analysed by the chi-squared test. Normally distributed continuous variables will be presented as mean and standard deviation (SD) and compared using Student’s *t* test; non-normally distributed variables will be expressed as median and interquartile ranges and analysed using the Mann–Whitney U test. A two-sided significance level of 0.05 will be used.

Baseline data such as age and GCS score at admission will be tested for any imbalance. If imbalances are detected, those factors will be corrected using a multiple logistic regression model.

The primary endpoint, namely the percentage of patients regaining consciousness 6 months after injury, will be presented as total percentage per group and analysed as categorical variables. The secondary outcome variables describing clinical status throughout the treatment and follow-up will be analysed as continuous variables.

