This trial has some novel features compared with other major RMNS trials. First, it is an Asian multicentre randomised controlled trial. The previous trials only focused on one region or even a single hospital. This trial is the first to widen the scope to a whole continent, reducing selection bias to a great extent. Second, in this trial, the RMNS therapy starts at an early stage, 7–14 days after the injury. Research shows that the later the application of electrical stimulation, the longer the duration needed to obtain a similar outcome [14]. Earlier commencement of neuroresuscitation treatment can show more efficacy, as long as the patient is stable. Third, the ACES trial uses various kinds of assessment scales to evaluate the condition of participants. The assessments fall into two groups: recovery pace parameters and long-term outcome parameters. The former group includes the GCS, GMS and FOUR. The GCS includes eye opening, verbal and motor responses. It has been used ubiquitously in acute care databases and in studies of acute neurologic injury. However, the GCS has been deficient in measuring key components of neurologic examination used for prognostication and most conspicuously lacks assessment of the brainstem reflexes. The FOUR score has been developed to overcome these inadequacies. It consists of four components that evaluate eye responses, motor responses, brainstem reflexes and respiration patterns. Because of its greater neurologic detail, the FOUR score is of more benefit than the GCS in predicting mortality in the ICU. A recent large multicentre prospective study in critically ill patients found an excellent inter-rater agreement between paired clinicians [36–38]. The long-term outcome parameters are the CRS-R, DRS and GOSE. The CRS-R is a standardised neurobehavioural assessment tool comprising six hierarchically organised subscales (auditory, visual, motor, oromotor–verbal, communication and arousal). Scores range from 0 to 23, with higher scores indicating a higher level of neurobehavioural function [1]. The DRS, a measure of functional outcome, includes measures of eye opening, verbalisation and motor response; cognitive understanding of feeding, dressing and grooming; degree of assistance and supervision required; and employability. Scores range from 0 to 29, with higher values indicating greater disability [1, 39]. The GOSE has eight ordered categories: death, vegetative state, lower severe disability, upper severe disability, lower moderate disability, upper moderate disability, lower good recovery and upper good recovery. It was developed as an extended version of the GOS in response to the perceived lack of sensitivity of the latter. It is now the primary outcome measure in trials of TBI [40]. Using all these scales, we hope to evaluate the condition of the coma patients as thoroughly as possible.

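### The only stated safety window runs to 6 months although stimulation lasts 2 weeks; a pre-stated comparison over the treatment period should be added beside it

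*Protocol article*

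**What the plan says.** Study endpoint in the protocol article sets the safety measure: "The safety of RMNS will be assessed by the incidence of adverse events within 6 months post injury". It names event types without closing the list: "including but not limited to (1) seizures, (2) increased intracranial pressure and (3) intracranial bleeding".

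Exposure is much shorter. Treatment protocol says "The electrical stimulation treatment will last for 8 h per day for 2 weeks", and the Discussion says "RMNS therapy starts at an early stage, 7–14 days after the injury".

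Data collection and follow-up describes the capture of events in two sentences. For the stimulation period: "Any complications will also be observed and recorded during the treatment". For the time afterwards: "Complications during follow-up will also be assessed".

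Statistical analysis adds only the general rule "Categorical variables will be described as numbers and percentages and analysed by the chi-squared test", with no time window for adverse events. Data management refers to a predetermined statistical analysis plan, which is not available here.

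**The concern.** The abstract makes safety a stated aim beside efficacy. The window fixed for it is about twelve times as long as the exposure. Seizures, raised intracranial pressure and intracranial bleeding can plausibly also occur after severe brain injury without stimulation, and such events would add to both arms for months after the current is switched off. A patient with an event on stimulation and a patient with an event at month 5 then contribute equally to a 6-month incidence.

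At stake is how a null result is read. The trial could report similar 6-month incidences and take this as support for safety while its own data held an excess during the 2 treatment weeks. A treatment-period comparison chosen after the data are seen would carry less weight than one stated beforehand.

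**Working it through.** The plan gives no rate, hypothesis or power for safety, so there is no figure of its own to reproduce. All event rates below are assumptions.

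**Inputs from the protocol article**
- 190 patients per group (Sample size justification: "a sample size of 380 in total (190 for each group) has therefore been chosen").
- Two-sided 0.05 and a chi-squared test (Statistical analysis).
- Stimulation for 14 days, starting 7 to 14 days after injury.

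**Share of the window under exposure**

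Take 6 months as 182.6 days and assume that stimulation starts at randomisation.
- Start on day 7: 14 / (182.6 − 7) = 14 / 175.6 = 8.0%, with 182.6 − 21 = 161.6 days after treatment.
- Start on day 14: 14 / (182.6 − 14) = 14 / 168.6 = 8.3%, with 182.6 − 28 = 154.6 days after treatment.

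**Dilution**

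Let p be the 2-week risk in an arm and b the later background risk, the same in both arms. Deaths and losses to follow-up are ignored. Then

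6-month risk = 1 − (1 − p)(1 − b).

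The difference between the arms becomes (p_stim − p_control)(1 − b), so the absolute excess shrinks only slightly. The risk ratio moves towards 1, and the larger background adds variance.

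**Power**

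Normal approximation with pooled variance under the null, p̄ being the mean of the two risks:

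power = Φ{[d − 1.96·√(2p̄(1 − p̄)/190)] / √([p₁(1 − p₁) + p₂(1 − p₂)]/190)}.

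- Treatment period, 8% vs 2%: d = 0.06, p̄ = 0.05, (0.06 − 1.96 × 0.02236) / 0.02215 = 0.73, power 77%.
- Six months with b = 10%: 1 − 0.98 × 0.90 = 11.8% and 1 − 0.92 × 0.90 = 17.2%; d = 0.054, p̄ = 0.145, (0.054 − 1.96 × 0.03612) / 0.03602 = −0.47, power 32%.

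**8% vs 2% on treatment, range of later risk**

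| Later risk b | 6-month risk, control | 6-month risk, stimulation | Risk ratio | Power |
|---|---|---|---|---|
| none (treatment period only) | 2.0% | 8.0% | 4.0 | 77% |
| 1% | 3.0% | 8.9% | 3.0 | 69% |
| 2% | 4.0% | 9.8% | 2.5 | 62% |
| 3% | 4.9% | 10.8% | 2.2 | 56% |
| 5% | 6.9% | 12.6% | 1.8 | 46% |
| 10% | 11.8% | 17.2% | 1.5 | 32% |
| 20% | 21.6% | 26.4% | 1.2 | 19% |

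**Other assumed on-treatment risks**

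| Stimulation vs control | Treatment period | 6 months, b = 10% | 6 months, b = 20% |
|---|---|---|---|
| 15% vs 5% | 90% | 61% | 41% |
| 30% vs 10% | near 100% | 98% | 90% |
| 6% vs 3% | 29% | 11% | 8% |

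The direction is the same throughout. The size runs from slight to severe. For a small excess such as 6% vs 3%, neither window is reliable.

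**The case against.** The strongest defence is that the sentence in Study endpoint sets how long events are counted. It does not say that timing will be ignored. Tabulating adverse events by period is work that a protocol often leaves to the analysis plan, and that plan is not shown. This stands in part. One cannot say that the trial will make no treatment-period comparison. It can be said that the endpoint as written names one window, and that this is the window to which readers will hold the trial.

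A reader might infer that everything is pooled into a single adverse-event figure and that an acute harm would be buried. The documents do not support that. Event types are named separately, the background for one type may be well below that for any event, and complications are to be recorded during treatment, so the comparison stays possible.

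A reader might also conclude that 6 months is the wrong window and should give way to 14 days. This is not supported either. The Discussion proposes mechanisms, such as neurotrophic and synaptic changes, that need not end with the current. If benefit can persist, so can harm, and a randomised comparison over full follow-up is a legitimate way to look for it. That harm arises mainly during stimulation is a reasonable premise that the documents do not establish.

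Finally, the plan sets no power target for safety. Power serves here only to measure sensitivity.

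**Conclusion.** The point holds in a limited form. The single stated safety window is poorly matched to a 2-week exposure, and it loses sensitivity to a harm confined to that exposure. Under an assumed 8% vs 2% on treatment with 190 per arm, power falls from 77% to between about 69% (later risk 1%) and 19% (later risk 20%). The loss is small if the background is low or the harm is large: 30% vs 10% keeps 98% power with a later risk of 10%. These figures rest on assumed rates, on equal later risk in both arms, and on harm arising mainly during stimulation. It is a worthwhile low-cost improvement and does not make the stated endpoint wrong.

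**What to change.** In Study endpoint, keep the 6-month comparison and add, stated in advance and for each named event type, the proportion of patients with at least one event from randomisation to the end of day 14. Use the same clock in both arms, so that control patients are counted over the same days as stimulated patients. Show day 15 to 6 months separately.

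The layout of the case report form is not shown. If it does not already separate the two periods, record the date of each event.

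The cost is one more table, more comparisons to interpret, and fewer events in the short window. Because the 6-month comparison is retained, late harm is not given less weight.

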### Data collection and follow-up

General baseline information will be collected about patients when they are sent to the emergency room and will include the following: demographics, time of admission, cause of injury, whether accompanied by multiple trauma, injury severity score, initial GCS score, initial intracranial computed tomography (CT) data including Marshall score and whether complicated by subarachnoid haemorrhage, pupillary light reflex or the need of craniotomy.

After 7–14 days of standard treatment, when the patient’s condition is stable and once he/she is enrolled and randomised, additional data will be collected, including vital signs such as blood pressure, heart rate, respiratory rate and oxygen saturation, pupillary light reflex and GCS, FOUR, CRS-R and DRS scores.

Patients in both the RMNS group and the sham group will be evaluated via GCS and FOUR scores at day 1 and day 7 of the treatment. Whether or not the coma patient regains consciousness and the date will be recorded in the CRF. Any complications will also be observed and recorded during the treatment.

Outcome assessment will be performed using the GCS, FOUR, CRS-R, DRS and GOSE at 1, 3 and 6 months. Complications during follow-up will also be assessed. If the patient is still in the hospital, the investigator may visit the patient on the ward to go through the evaluation. If the patient has been discharged, his or her legal representative will be told to come back in due time for assessment after leaving the hospital. If the patient does not arrive, the investigator will try to contact the patient or the family members by telephone. Other possible methods may also be used to explain the situation and complete the outcome assessment. If all attempts fail, no further contact will be made, and the patient will be recorded as lost to follow-up. Any death occurring either in or out of the hospital will be recorded and possible causes explored.

All the data will be collected by independent investigators who are blind to the patient’s allocation. Each local study centre will assign a specific investigator at the beginning of the trial. This investigator will be excluded throughout treatment of all the participants unless asked to do the assessment by clinicians. During the 2 weeks of RMNS treatment, the investigators will be asked to collect the data during the interval of 8-h RMNS treatment per day so as to eliminate any chance of disclosing the allocation.

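### The rule that ends contact after failed attempts is not limited to the 6-month visit, so read literally it bars the primary assessment for a patient unreachable at 1 or 3 months

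*Protocol article*

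**What the plan says.** All of the contact rules are in the protocol article, Data collection and follow-up, in a single paragraph. It opens with the schedule: "Outcome assessment will be performed using the GCS, FOUR, CRS-R, DRS and GOSE at 1, 3 and 6 months". Discharged patients are asked to return. For those who do not, there are two further steps: "If the patient does not arrive, the investigator will try to contact the patient or the family members by telephone", and then "Other possible methods may also be used to explain the situation and complete the outcome assessment". The rule in question follows: "If all attempts fail, no further contact will be made, and the patient will be recorded as lost to follow-up". The paragraph closes with deaths: "Any death occurring either in or out of the hospital will be recorded and possible causes explored".

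Two statements under Study endpoint fix what is needed at 6 months. For efficacy: "The primary endpoint is the percentage of patients regaining consciousness 6 months after injury". For safety: "The safety of RMNS will be assessed by the incidence of adverse events within 6 months post injury". In the same section the scores at 28 days and 3 months appear only among the secondary endpoints.

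**The concern.** This is a stated rule, not a gap that a fuller document might fill. It gives a status to the patient, not to the visit, and the bar on contact has no end date. A site that follows the words would close a patient who could not be found at 1 or 3 months and would not try at 6 months.

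Three things are then at stake.

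- The primary outcome exists at one time only. Failure to collect a secondary score could remove it, although a later call might have obtained it.
- Adverse events are to be counted to 6 months. Closing a patient earlier cuts that window short.
- Deaths are to be recorded wherever they occur, but no source is named for a patient whom nobody may contact.

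An analysis plan can choose how to treat missing outcomes, but it cannot recover outcomes that were never sought. Under Data management, each case report form is checked and sent to the coordinating centre only after 6-month follow-up is done. By that route, an early closure would come to light too late to correct.

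**Working it through.** **Reading the text.** The rule applies only after a missed return visit, failed telephone contact with patient or family, and possibly failed other methods. It stands in the paragraph that covers all three assessments and names none of them. Nothing in the article says that contact is tried again at the next assessment.

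**The plan's own figure.** None is given for the rule, and no expected loss rate is stated. The nearest figure is the allowance implied under Sample size justification: 380 − 334 = 46 patients, and 46/380 = 12.1%. Whether 334 is itself correct is a separate matter and does not affect the counts below.

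**Illustration (assumed inputs).** Let p be the chance that a patient is unreachable at any one assessment, equal and independent across assessments. Let k be the number of assessments at which the rule can bite, counting the 6-month one.

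- Loss of the primary outcome under the literal rule: 1 − (1 − p)^k
- Loss if contact is tried again at 6 months: p

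The case k = 3 exposes all three assessments. The case k = 2 exposes only those at 3 and 6 months, which fits if nearly all patients are still in hospital at 1 month. Counts are out of 380.

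| p | Rule, k = 3 | Rule, k = 2 | Retry at 6 months |
|---|---|---|---|
| 3% | 1 − 0.97³ = 8.7% (33) | 1 − 0.97² = 5.9% (22) | 3% (11) |
| 5% | 1 − 0.95³ = 14.3% (54) | 1 − 0.95² = 9.75% (37) | 5% (19) |
| 10% | 1 − 0.90³ = 27.1% (103) | 1 − 0.90² = 19.0% (72) | 10% (38) |

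At p = 5% the rule therefore costs 54 − 19 = 35 primary outcomes with k = 3, or 37 − 19 = 18 with k = 2.

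**Allowing for correlation.** Patients hard to find once are likely to be hard to find again. Suppose half of those unreachable at one assessment are also unreachable at another, with p = 5%.

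- k = 2: excess = 0.05 × 0.5 = 2.5%, or 9.5 of 380; total loss 7.5%.
- k = 3: missed at 1 or 3 months = 0.05 + 0.05 − 0.025 = 7.5% (about 28). If half of these could be reached at 6 months, the excess is 3.75% (about 14) and total loss 8.75% (about 33).

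The excess falls to zero only if nobody missed early could ever be reached later.

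**Against the allowance.** Under independence, total loss reaches 12.1% at p of about 4.2% with k = 3, since 1 − (334/380)^(1/3) = 0.042. With k = 2 it does so at about 6.2%, since 1 − (334/380)^(1/2) = 0.062. In the first case 0.042 × 380 = 16 patients would be lost with or without the rule. The rule adds 46 − 16 = 30, or 7.9 points.

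**The case against.** The strongest reply is that the literal reading was not meant. The sentence just before the rule speaks of completing the outcome assessment, in the singular, so the attempts that fail may be those for one visit. The rule may also be meant only for the end of follow-up. Both readings are possible. But the status is given to the patient and the bar on contact has no limit, so the milder readings need words that are not there. Sixteen centres have to apply the sentence as it stands. This reply lowers confidence without removing the point.

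A second reply concerns timing. Enrolment comes 7 to 14 days after admission and treatment lasts 2 weeks, ending around day 21 to 28, and the first follow-up assessment is at 28 days. Few patients may be both discharged and out of contact by then. That is fair, and it makes k = 2 the more cautious case. At p = 5% its loss of 9.75% lies inside the implied allowance.

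Several stronger inferences are tempting, and the documents do not support them.

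- *A single failed call ends follow-up.* It does not. All routes must fail first.
- *Later deaths will go unseen.* The next sentence requires them to be recorded. What is missing is a stated route once contact has stopped.
- *The rule contradicts the intention-to-treat analysis.* The sentence "All randomised patients will be included in their original assigned group regardless of the actual treatment approach they receive" governs group assignment when treatment departs from plan. It says nothing on obtaining outcomes, so a lost outcome does not contradict it.
- *The rule by itself exhausts the allowance for loss at p = 4.2%.* It accounts for 7.9 of the 12.1 points; the rest would be lost anyway.
- *The loss biases the comparison.* Being out of contact could go with waking, with remaining vegetative or with death, and these pull in different directions. The rule is the same in both arms. Loss that depends on outcome or arm is plausible but not shown.

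**Conclusion.** The point holds as a defect of wording with a real consequence. Followed literally, the rule turns failure to reach a patient at a secondary assessment into loss of the primary outcome, ends adverse-event follow-up early, and leaves no stated means of meeting the requirement to record deaths.

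The size cannot be known from the documents. With p = 5% and independence, avoidable loss is 18 to 35 of 380 patients, depending on whether the 1-month assessment is exposed. With the 50% dependence assumed above it is about 10 to 14. Both ranges rest on an assumed p and on sites applying the rule as written. The matter is a cheap improvement, held with moderate confidence because a per-visit or end-of-follow-up reading cannot be excluded. The documents do not show that the trial's result would be biased.

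**What to change.** Make the rule visit-specific, in the protocol and in the instructions to sites. Suggested wording:

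*If all attempts fail, that visit is recorded as missed. Contact is attempted again at every later visit, and always at 6 months. A patient is recorded as lost to follow-up only if the 6-month status, including whether the patient is alive, cannot be obtained. Patients for whom consent to contact has been withdrawn are not contacted.*

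The same amendment should name the source for deaths among patients who miss visits.

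The cost is a short amendment and a few more calls, with no new visits or staff. The article states that recruitment is under way, so patients not yet at 6 months would benefit. Any patient already closed at 1 or 3 months could be reopened for the 6-month attempt if consent to contact still stands.
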